**Figure 1 F1:**
[figure not shown]
UK Mini Mitral Trial flow diagram. EQ-5D-5L, EuroQol 5 Dimension 5 Level; SF-36v2, Short Form Health Survey.

### SF-36v2 and EQ-5D-5L

Physical functioning and overall quality of life are assessed using SF-36v2 and EQ-5D-5L^42–45 51^ questionnaires administered prior to randomisation. Questionnaire completion is repeated over the telephone at 6, 12, 18, 24, 38 and 52 weeks following index surgery.

### Echocardiogram

Cardiac function is assessed via TTE at baseline, post operatively (1 day to 12 weeks) and at 52 weeks. Measurements of left ventricular volumes, dimensions and function, mitral regurgitation severity and estimates of right heart function and pulmonary artery pressure are reported.

### Accelerometer

Levels of physical activity and quality of sleep are quantified using accelerometer measures. Accelerometers are worn on patients’ non-dominant wrist nonstop for 7 consecutive days at seven timepoints (baseline, 6, 12, 18, 24, 38 and 52 weeks following index surgery). The restrictions of movement by being an inpatient means accelerometer measures are not possible for inhouse urgent patients and are not to be undertaken.

### Statistical analysis

Primary analysis will follow intention to treat principles, with patients analysed according to randomisation, irrespective of surgical intervention received. A full statistical analysis plan will be developed and agreed with the Independent Data Monitoring and Ethics Committee (IDMEC) and TSC prior to the end of data collection.

Outcome data will be analysed at the end of the study; no interim outcome analyses are planned.

Primary analysis of change in physical functioning, measured using SF-36v2 at 12 weeks, will use a general linear model accounting for surgical intervention, baseline scores, valve pathology and concomitant surgery. Robust SE will account for intrapatient correlation due to repeated measures. A similar modelling approach will be used for the final analysis of change in physical functioning at 52 weeks.

Secondary outcomes: continuous outcomes will be analysed using a general linear model, binary outcomes will be analysed using a generalised estimating equation to account for repeated binary data over time, categorical outcomes (with more than two categories) will be analysed using baseline-category logit model, while log-rank test and frailty modelling will be used to analyse time-to-event outcomes. Analysis of all outcomes with repeated measures on the same patient will account for intrapatient correlation. Multiple imputation for secondary outcomes will be used if necessary to sensitise incomplete data. All outcomes will also be described using simple statistics to facilitate interpretation and communication of findings. Secondary analysis will also include hierarchical modelling of patients, surgeons and centres, to provide an estimate of treatment effect at each of these levels.

Each question within the SF-36v2 physical functioning scale will be scored based on the RAND scoring system.^42^ The average of the per-patient scale scores (assuming each question carries equal weight) will provide the primary outcome for physical functioning at 12 weeks.

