### Setting

Three hundred and sixteen patients due to receive MVr surgery will be recruited from UK NHS cardiothoracic surgery units with established minimally invasive and conventional mitral valve services. All centres will be able to accommodate the needs of this trial including established minimally invasive MVr services, research nurse and echocardiographer support, and facilities to carry out trial assessments. Only units in equipoise in the way they manage their patients requiring MVr will participate.

At each centre, individual surgeons perform one type of operation; MVr via thoracoscopically guided right minithoracotomy or MVr via median sternotomy. Before performing surgery within the trial, each surgeon has completed 50 of these; the Trial Steering Committee (TSC) reviews a record of the number of operations for each surgeon, and agrees to their participation, in advance of them doing so. Depending on their allocation, patients can be required to move to another surgeon following randomisation.

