#### Inclusion criteria

Adult (≥18 years old at consent) with degenerative mitral valve disease, requiring MVr*.Written informed consent.Fit for cardiac surgery and cardiopulmonary bypass.

*Patients requiring concomitant surgery for atrial fibrillation (AF), tricuspid valve repair, and/or patent foramen ovale (PFO) closure are included

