### Randomisation

Eligible patients will be randomised in a 1:1 ratio to undergo MVr using minimally invasive thoracoscopically guided right minithoracotomy (intervention under study) or conventional median sternotomy (control arm/usual care) by members of the research team at each centre using a 24-hour, central, secure, web-based randomisation system with concealed allocation (procured from Sealed Envelope).

Randomisation is performed using a minimisation scheme, which adjusts for baseline SF-36v2 physical functioning score, presence or absence of AF and/or PFO, and presence and severity of tricuspid regurgitation.

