### Sample size

The primary outcome measure is change in physical functioning scale within SF-36v2^42^ from baseline to 12 weeks following index surgery. On the basis of the literature and consulting with cardiac and patient communities, a minimally clinically important difference is 10 points on the scale. UK Mini Mitral is powered to investigate the superiority of thoracoscopically guided right minithoracotomy over conventional sternotomy.

One study^31^ reports a small variation (SD of 8) in SF-36 physical function scores; this is not seen in other studies^32 33^ which report a SD of 30. We used the conservative estimate to inform the original sample size calculation:

Assuming alpha of 5% and 90% power, 382 patients (191 in each arm) would be required to detect a minimally clinically important difference of 10 points in the SF-36v2^42^ physical functioning scale at 12 weeks (assuming SD of 30); allowing for attrition, we planned to randomise 400 patients. To assess our assumptions, we performed a blinded sample size re-estimation using baseline SF-36v2 physical functioning scale data from 177 trial patients. Using the re-estimated SD of 26.3 with 90% power, 288 patients are required to detect a 10 point difference in SF-36v2 physical functioning at 12 weeks. Accounting for 10% attrition, 316 patients will be recruited.

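### The stated primary model does not match the minimisation scheme: AF/PFO and tricuspid regurgitation are left out, and concomitant surgery stands in their place without being tied to the plan made before randomisation

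*Protocol article*

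**What the plan says.** All references are to the protocol article.

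- *Statistical analysis*: the primary analysis "will use a general linear model accounting for surgical intervention, baseline scores, valve pathology and concomitant surgery". It follows intention to treat, "with patients analysed according to randomisation, irrespective of surgical intervention received". On standard errors: "Robust SE will account for intrapatient correlation due to repeated measures".
- *Randomisation*: the minimisation scheme "adjusts for baseline SF-36v2 physical functioning score, presence or absence of AF and/or PFO, and presence and severity of tricuspid regurgitation".
- *Inclusion criteria*: "Patients requiring concomitant surgery for atrial fibrillation (AF), tricuspid valve repair, and/or patent foramen ovale (PFO) closure are included". The exclusion criteria rule out any other concomitant cardiac surgery.
- *Setting*: "individual surgeons perform one type of operation; MVr via thoracoscopically guided right minithoracotomy or MVr via median sternotomy". A patient may have to change surgeon after allocation.

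The article defers a full statistical analysis plan to a later document, which is not at hand.

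**The concern.** Only the baseline score is in both lists. AF, PFO and tricuspid regurgitation are recorded before allocation and are the indications for the three permitted additional procedures. The model names the procedures and not the indications.

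That matters because the indication is fixed at baseline, while the procedure need not be. If the term is coded from the operation record, it is measured after allocation, and surgeons who work by only one route decide whether the procedure is done. A difference in procedure rates between arms would then be partly a consequence of allocation. Conditioning on it would do two things: remove any effect of the approach that runs through the added procedure, and compare patients of unequal severity within each level of the term. Neither fits the intention-to-treat aim.

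The two codings therefore estimate different quantities, and the printed text allows both. In a superiority trial the primary model should not leave that choice open until data are available.

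**Working it through.** **1. The plan's own figure.** The article states: "Assuming alpha of 5% and 90% power, 382 patients (191 in each arm) would be required" for a 10-point difference, "assuming SD of 30". Per arm, n = 2(1.960 + 1.282)² × SD² / 10².

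- SD 30: 189.1, so 190 per arm and 380 in total (stated: 382).
- SD 26.3: 145.4, so 146 per arm and 292 in total (stated: 288).

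Both agree within 2%. Neither depends on the covariate list.

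**2. Scale of the standard error.** With 144 per arm, the unadjusted SE is 26.3 × √(2/144) = 3.10. With an assumed baseline-to-outcome correlation of 0.5 it is 3.10 × √0.75 = 2.68.

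**3. Formula for the shift.** In a linear model the adjusted effect equals the total effect minus b × (p₁ − p₀). Here p₁ and p₀ are the proportions having a concomitant procedure in the minithoracotomy and sternotomy arms, and b is the within-arm difference in outcome between patients with and without one. Equal proportions give no shift.

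**4. Numbers put in.** The article gives no procedure rates or effects, so every input here is assumed: AF 30%; tricuspid regurgitation in three grades at 50/30/20%; AF costs 8 points; each regurgitation grade costs 5 points. A procedure is indicated by AF or the top grade, so in 0.30 + 0.70 × 0.20 = 44% of patients.

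- Mean burden if indicated: 8 × 0.30/0.44 + 5 × 0.49/0.44 = 11.02 points, where 0.49 = 0.30 × 0.70 + 0.14 × 2. If not indicated: 5 × 0.30/0.80 = 1.88 points.
- Suppose 90% of indicated sternotomy patients and 60% of indicated minithoracotomy patients have the procedure. Then p₀ = 0.396, p₁ = 0.264 and p₁ − p₀ = −0.132.
- Mean burden without a procedure is (0.044 × 11.02 + 0.56 × 1.88)/0.604 = 2.54 under sternotomy and (0.176 × 11.02 + 0.56 × 1.88)/0.736 = 4.06 under minithoracotomy. The within-arm gaps are 8.48 and 6.96. Weighted by p(1 − p), which is 0.239 and 0.194, they average 7.80, so b = −7.80.
- If the procedure itself costs 0, 5 or 10 points, the shift is −0.132 × 7.80, 12.80 or 17.80 = −1.0, −1.7 or −2.3 points.
- With 90% against 80%, p₁ − p₀ = −0.044. The same steps give b = −8.20 before the procedure's own cost. With a 5-point cost the shift is −0.044 × 13.20 = −0.6.

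**5. Simulation of the same set-up** (288 patients, 2,000 replicates, minimisation with an assumed probability of 0.8, ordinary least squares at one time point):

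| Procedure done if indicated (sternotomy / minithoracotomy) | Procedure cost | True total effect | Model with performed surgery | Model with AF and regurgitation |
|---|---|---|---|---|
| 90% / 90% | 5 | 10.00 | 9.96 | 9.95 |
| 90% / 80% | 5 | 10.22 | 9.56 | 10.14 |
| 90% / 60% | 0 | 10.00 | 9.01 | 10.03 |
| 90% / 60% | 5 | 10.66 | 8.91 | 10.60 |
| 90% / 60% | 10 | 11.32 | 8.98 | 11.36 |

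The true total is 10 plus cost × (p₀ − p₁); for example, 10 + 5 × 0.132 = 10.66. The shifts in the performed-surgery model are about 0, −0.7, −1.0, −1.8 and −2.3, in line with the formula. With a true total effect of zero, that model rejected in 5.1% of replicates at equal rates and 5.9% at 90%/60% with no procedure cost.

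**6. A second assumed route, through unmeasured severity.** Severity is worth 8 points per SD and correlates 0.5 with the decision to add a procedure. With overall rates of 40% and 25%, b = −(0.386 + 0.318)/(0.240 + 0.1875) × 0.5 × 8 = −6.59. The shift is −0.15 × 6.59 = −1.0, or −0.15 × 11.59 = −1.7 if the procedure also costs 5 points. At 40% and 35% it is −0.3 to −0.6.

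**7. Leaving out AF/PFO and regurgitation.** With arm and baseline score only, the estimate stayed centred on the total effect. The model SE averaged 2.76 to 2.90 against an empirical 2.62 to 2.71, so it errs on the conservative side. With the concomitant term included it was 2.72 to 2.76 against 2.61 to 2.73, which is about right or slightly large.

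**The case against.** The strongest reply is that nothing in the article says performed. The inclusion criteria speak of patients who need the additional surgery, and the exclusion of other concomitant surgery can be applied only if the plan is known at eligibility. On that reading the covariate is a baseline variable and there is no bias. This stands, and a reader who inferred that the model certainly adjusts for a post-randomisation variable would go beyond the text. Equally, the analysis section attaches the word baseline to the scores and not to the surgery, so the planned reading is not fixed either.

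A reader might also infer that the model ignores the minimisation factors. It does not: the baseline score is included, and concomitant surgery partly stands in for the other two. Nor do the omissions make the inference invalid, since they cause no bias and at most a slightly large SE.

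Valve pathology raises the same question only if it is graded at operation. The schedule of events lists transthoracic and transoesophageal echocardiography at baseline, and nothing says that pathology is taken from the operation.

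Finally, coding details often belong in the statistical analysis plan. That is fair for planned versus performed, and the later plan may already settle it. It does not remove the mismatch between two lists that the article itself prints.

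**Conclusion.** The point holds as a mismatch between the design and the stated primary model, together with one loosely defined covariate. It is worth correcting but is not a demonstrated error in the estimate.

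Bias needs two conditions: the term is coded as performed, and procedure rates differ by arm. Surgeons working by one approach make the second possible; the article offers no evidence that it happens, or in which direction. A higher procedure rate under minithoracotomy would reverse the sign of the shifts shown. Their size, from 0 to roughly 2 points on a 10-point target, rests wholly on assumed inputs, and even the largest is below one standard error (about 2.7 points).

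The documents do not support saying that the trial's estimate is biased or that its standard errors are wrong.

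**What to change.** In the statistical analysis plan, and in the protocol at its next revision, state that the primary model adjusts for the minimisation factors as recorded at randomisation: baseline SF-36v2 physical functioning, AF and/or PFO, and tricuspid regurgitation severity. Then:

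- drop concomitant surgery, or define it strictly as planned before randomisation. Adding AF/PFO and regurgitation while keeping surgery as performed would not be enough, because any effect running through the procedure would still be removed;
- if valve pathology is kept, take it from baseline imaging;
- report the procedures actually performed descriptively by arm.

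Adding centre is optional: it is not a listed minimisation factor, and hierarchical modelling of surgeons and centres is already planned as a secondary analysis.

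The cost is one sentence and a few degrees of freedom. The minimisation variables are already held in the randomisation system, and the sample size is unchanged. The wording should be settled before outcome data are seen by arm.

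### Surgeon is nested within arm, but the primary model ignores surgeon, so its confidence interval is too narrow if outcomes vary between surgeons; a power shortfall is possible but not established.

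*Protocol article*

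**What the plan says.** The Setting section of the protocol article fixes the design feature that matters: "At each centre, individual surgeons perform one type of operation". Patients may have to change surgeon after randomisation to receive their allocated operation.

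The Statistical analysis section lists the terms of the primary model for the 12-week SF-36v2 physical functioning score: surgical intervention, baseline score, valve pathology and concomitant surgery. On the standard error it says: "Robust SE will account for intrapatient correlation due to repeated measures". Surgeon and centre appear only in a later sentence of that section: "Secondary analysis will also include hierarchical modelling of patients, surgeons and centres, to provide an estimate of treatment effect at each of these levels".

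The Sample size section is a comparison of two means. It takes the target difference as "a minimally clinically important difference is 10 points on the scale", and the current figure reads "Using the re-estimated SD of 26.3 with 90% power, 288 patients are required to detect a 10 point difference". Attrition of 10% brings recruitment to 316. No surgeon ICC, caseload or design effect is given.

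**The concern.** Patients are randomised individually, but allocation also decides which group of surgeons may operate. Apart from crossovers, all patients of one surgeon are in the same arm. A surgeon whose patients recover better or worse than average therefore shifts one arm only, and the shift does not cancel in the treatment contrast. The variance of the contrast then has a between-surgeon part, as in a cluster trial. A robust standard error that groups observations by patient does not capture it.

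The confirmatory p-value and confidence interval would come from this model. A superiority claim for minithoracotomy could then look more certain than the data allow, because part of the difference may belong to the surgeons who happened to be in each arm.

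There is also a smaller wording problem. The secondary analysis promises a treatment effect at surgeon level. As no surgeon performs both operations, a within-surgeon treatment effect cannot be estimated.

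**Working it through.** **1. Reproduce the plan's sample size.** Inputs from the Sample size section: difference 10, SD 30 (original) or 26.3 (current), alpha 5%, power 90%. Sidedness is not stated. Two-sided is assumed, because with SD 26.3 a one-sided test would need only about 238 patients in total.

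- Formula: n per arm = 2 × (1.96 + 1.2816)² × SD² / 10².
- SD 30: 189.1, rounded up to 190 per arm, or 380 (382 with the t distribution). Stated: 382.
- SD 26.3: 145.4, rounded up to 146 per arm, or 292 (294 with the t distribution). Stated: 288.
- Power at 288: SE = 26.3 × √(4/288) = 3.10; Φ(10/3.10 − 1.96) = 89.7%.

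The stated figures reproduce within rounding, and they do so with ICC = 0. The calculation holds nothing in reserve for clustering.

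**2. Add surgeon clustering.** 284 patients are analysed (316 × 0.9 = 284.4). The number of surgeons k (26 to 40 in total) and the ICC (0.005 to 0.05) are assumptions; the document gives neither. With m = 284/k patients per surgeon:

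- Design effect DE = 1 + (m − 1) × ICC.
- Type I error of the test that ignores surgeon = 2 × [1 − Φ(1.96/√DE)].
- Power with a correct SE, no gain from baseline = Φ(10 / (26.3 × √(4/284) × √DE) − 1.96).

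| k | m | ICC | DE | Type I error | Power, SD 26.3 |
|---|---|---|---|---|---|
| any | – | 0 | 1.00 | 5.0% | 89.3% |
| 40 | 7.1 | 0.005 | 1.03 | 5.4% | 88.4% |
| 40 | 7.1 | 0.01 | 1.06 | 5.7% | 87.5% |
| 40 | 7.1 | 0.02 | 1.12 | 6.4% | 85.6% |
| 40 | 7.1 | 0.05 | 1.30 | 8.6% | 80.1% |
| 26 | 10.9 | 0.005 | 1.05 | 5.6% | 87.8% |
| 26 | 10.9 | 0.01 | 1.10 | 6.2% | 86.3% |
| 26 | 10.9 | 0.02 | 1.20 | 7.3% | 83.3% |
| 26 | 10.9 | 0.05 | 1.50 | 10.9% | 74.5% |

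The SE that ignores surgeon is too small by the factor √DE, which is 1.02 to 1.22 in this table. The formula assumes equal caseloads. Unequal caseloads or fewer surgeons make the inflation larger: with 20 surgeons at ICC 0.02 the type I error is 8.1%.

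**3. Allow for baseline adjustment.** The SD of 26.3 comes from a "blinded sample size re-estimation using baseline SF-36v2 physical functioning scale data from 177 trial patients", so it is the spread of baseline scores and not the residual SD of the primary model. If r is the correlation between baseline and 12-week scores (not given, so assumed), the residual SD is 26.3 × √(1 − r²). Here the ICC is read as that of the residual.

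| r | ICC 0 | k=40, ICC 0.02 | k=40, ICC 0.05 | k=26, ICC 0.02 | k=26, ICC 0.05 |
|---|---|---|---|---|---|
| 0.3 | 91.9% | 88.7% | 83.6% | 86.6% | 78.4% |
| 0.5 | 95.9% | 93.7% | 89.9% | 92.2% | 85.6% |
| 0.6 | 98.0% | 96.6% | 93.9% | 95.5% | 90.6% |

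Power can fall on either side of 90%, depending on r as much as on the ICC. The type I error column in step 2 does not change with r at a given ICC, because the SE that ignores surgeon shrinks in the same proportion as the true one.

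**The case against.** The design limits variation between surgeons. Each has done at least 50 operations of the relevant type, and the Trial Steering Committee approves each one. Both operations are established at every centre, so effects shared by a centre largely cancel, and what counts is the surgeon within centre and arm. For patient-reported function at 12 weeks the ICC may be small: at 0.005 to 0.01 the type I error is only about 5.4% to 6.2%. The plan also prespecifies a hierarchical analysis, so a reader would see whether the result survives it, and a full statistical analysis plan is still to follow.

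Much of this stands as a limit on size. None of it shows that the ICC is 0. Nor is this a detail left to the later plan, because the article itself names the primary model and places surgeon in a secondary analysis.

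A reader might go further and infer that the advertised 90% power is overstated. The protocol does not support that as a flat statement. Step 3 shows that baseline adjustment, for which the sample size claims no gain, may offset the loss. A reader might also take the primary interval to be too narrow whatever the ICC; that holds only if the ICC is above 0.

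The sentence on treatment effects at each level can be read more loosely, as a treatment estimate that allows for each level. It does not affect the primary result.

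**Conclusion.** The point holds in conditional form. Surgeon is nested in arm and the primary model leaves it out, so for any surgeon ICC above 0 the primary interval is too narrow and the type I error exceeds 5%. The direction follows from the document; the size does not. With 284 analysed and an assumed 26 to 40 surgeons with equal caseloads, the type I error runs from about 5.4% to 6.2% (ICC 0.005 to 0.01) and from 6.4% to 10.9% (ICC 0.02 to 0.05).

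On the sample size's own inputs (SD 26.3, no gain from baseline), any positive ICC takes power below 90%. Whether actual power falls short is open: at an assumed correlation of 0.5 it is about 86% to 94% over ICC 0.02 to 0.05. That offset repairs neither the standard error nor the type I error, which is the firmer half of the point.

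**What to change.** 1. Make the clustered analysis primary: a linear mixed model with centre and a random intercept for surgeon, nested in centre and arm, with Kenward-Roger or Satterthwaite degrees of freedom. A surgeon-level cluster-robust standard error with a small-sample correction is an alternative. Surgeon cannot be a fixed effect, because it is nested in arm. State which surgeon defines the cluster for patients who cross over.
2. Restate power over a declared range of ICC, number of surgeons and baseline correlation, without changing enrolment.
3. Reword the secondary analysis to report a surgeon variance component (or ICC) and centre-by-treatment variation, and drop the surgeon-level treatment effect.

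The cost is mainly wording in the protocol and the analysis plan, which the article says is still to be developed. The schedule of events does not list the operating surgeon as a data item, but the hierarchical analysis already planned needs it. The downside is a somewhat wider confidence interval and a less favourable stated power if the ICC exceeds 0. With few surgeons the degrees-of-freedom correction adds to this: for 10 surgeons per arm, 288 evaluable, SD 26.3 and ICC 0.02, power is about 77% rather than 82%.

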**Methods and analysis:**

UK Mini Mitral is a multicentre, expertise based randomised controlled trial of minimally invasive thoracoscopically guided right minithoracotomy versus conventional sternotomy for MVr. The trial is taking place in NHS cardiothoracic centres in the UK with established minimally invasive mitral valve surgery programmes. In each centre, consenting and eligible patients are randomised to receive surgery performed by consultant surgeons who meet protocol-defined surgical expertise criteria. Patients are followed for 1 year, and consent to longer term follow-up.

Primary outcome is physical functioning 12 weeks following surgery, measured by change in Short Form Health Survey (SF-36v2) physical functioning scale. Early and 1 year echo data will be reported by a core laboratory. Estimates of key clinical and health economic outcomes will be reported up to 5 years.

The primary economic outcome is cost effectiveness, measured as incremental cost per quality-adjusted life year gained over 52 weeks following index surgery.

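### The secondary hierarchical analysis promises a treatment effect at surgeon level, but each surgeon performs one type of operation, so a surgeon-specific effect cannot be estimated

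*Protocol article*

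**What the plan says.** The protocol article, Statistical analysis, closes its paragraph on secondary outcomes with a commitment that begins "Secondary analysis will also include hierarchical modelling". It states the purpose as "hierarchical modelling of patients, surgeons and centres, to provide an estimate of treatment effect at each of these levels". Three levels are named, and a treatment effect is promised at each.

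The Setting section describes how surgeons relate to the two arms: "At each centre, individual surgeons perform one type of operation; MVr via thoracoscopically guided right minithoracotomy or MVr via median sternotomy". It adds: "Depending on their allocation, patients can be required to move to another surgeon following randomisation". The abstract gives the design its usual name: "UK Mini Mitral is a multicentre, expertise based randomised controlled trial".

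Centres are different. The Setting section says that patients are recruited from "UK NHS cardiothoracic surgery units with established minimally invasive and conventional mitral valve services", so both operations are available at every centre.

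**The concern.** A treatment effect at a given level of a hierarchy needs units at that level in which both treatments are observed. Centres meet this condition and surgeons do not. The analysis section therefore promises a quantity that the Setting section rules out.

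The risk lies in what would be reported if the sentence were followed literally. Mixed-model software may still return a figure for each surgeon. That figure would be either a comparison of different surgeons, in which skill and approach cannot be separated, or a shrunken prediction whose content comes from the model's assumptions. Labelled as a surgeon-level effect of the approach, it would mislead readers of a trial that is meant to inform commissioning and adoption.

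**Working it through.** The plan attaches no figure to this clause, so the check is structural: set the two sections side by side and ask what the planned data can identify.

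**Inputs**
- Surgeon and arm: one type of operation per surgeon (Setting), so surgeon is nested in arm.
- Centre and arm: both operations at every centre (Setting) and 1:1 randomisation (Randomisation), so arm is crossed with centre.
- The numbers of surgeons and centres are not given. The small numbers used below are illustrative, and the conclusion does not depend on them.

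**Step 1: write down the model that the clause implies.** For a patient of surgeon j in centre k, with T = 1 for minithoracotomy and T = 0 for sternotomy:

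Y = μ + τT + c_k + d_k·T + s_j + δ_j·T + error

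Here τ is the overall effect, c_k the centre effect, d_k the centre's departure from τ, s_j the surgeon's general performance and δ_j the surgeon's own departure from the treatment effect.

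**Step 2: see what each surgeon's data contain.**
- Minithoracotomy surgeon (always T = 1): expected mean = μ + τ + c_k + d_k + s_j + δ_j. Only the sum s_j + δ_j appears.
- Sternotomy surgeon (always T = 0): expected mean = μ + c_k + s_j. δ_j does not appear.
- Difference between two such surgeons in one centre, j and j′: (τ + d_k) + (s_j + δ_j − s_j′). The treatment effect comes mixed with the difference between two people.

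In no case can δ_j be isolated. More patients per surgeon would sharpen the sums without separating their parts.

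**Step 3: confirm by the rank of the design matrix.** Take S surgeons, each with an intercept column and a surgeon-by-treatment column. When surgeons are nested in arm, the second column equals the first for a minithoracotomy surgeon and is all zeros for a sternotomy surgeon. The rank is therefore S out of 2S.
- S = 4, two per arm: rank 4 of 8.
- The same four surgeons, if each did both operations: rank 8 of 8.
- Centre intercepts plus centre-specific treatment effects, three centres with both arms: rank 6 of 6.

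The loss is specific to the surgeon level. Centre effects are identified.

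**Step 4: ask whether random effects rescue it.** Treat s_j and δ_j as independent random terms with variances σ_s² and σ_δ². For a minithoracotomy surgeon, the predicted δ_j is the share σ_δ²/(σ_s² + σ_δ²) of that surgeon's shrunken deviation. The share can be obtained only by assuming that σ_s² is the same in both arms. For a sternotomy surgeon the predicted δ_j is zero, so the reported effect would simply repeat the centre's or the overall effect. The output would reflect the assumption, not evidence about that surgeon.

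**Step 5: list what remains estimable.** The overall effect τ remains, with surgeon as a random effect nested in arm, as does the effect within each centre. The between-surgeon variance within an arm can be estimated, and separated from centre-by-treatment variation, where at least some centres have two or more surgeons in an arm.

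**The case against.** The strongest defence is that the clause is only loosely worded. It could mean one treatment effect, estimated from a model that represents patients, surgeons and centres. Such an effect is estimable, and so are a between-surgeon contrast of the arms and a surgeon variance component. This stands as an account of what the authors may have intended. It does not match the text, which promises an estimate at each level. If the charitable reading is intended, the proposed wording says so.

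A second defence is that detail belongs in the full statistical analysis plan, which the article says will follow. That holds for an omission. Here a positive statement conflicts with the design, and a later plan could only drop or redefine the quantity.

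A third is that a surgeon might in practice have patients of both allocations. Under the stated rule, that could come about only through departures from allocation, which give no valid within-surgeon comparison.

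A reader might also draw three stronger conclusions, which the documents do not support:
- *That nothing at surgeon level can be learned.* The variance between surgeons and the arm contrast allowing for clustering by surgeon both remain.
- *That a patient-level effect is equally undefined.* In a multilevel model the patient level is the ordinary contrast between randomised patients, and the article promises no individual effects.
- *That centre-level effects form an uncontrolled family of subgroup tests.* The analysis is labelled secondary, and no centre-level tests, thresholds or conclusions are stated. Labelling and multiplicity are commonly left to the analysis plan. Any error rate or interval width for single centres would need an assumed number of centres and unpooled analyses, which a hierarchical model is not.

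**Conclusion.** The concern holds for the surgeon level only. As written, the Statistical analysis section promises an estimate that the Setting section makes unobtainable. The conclusion rests on the stated rule that each surgeon performs one type of operation. It needs no assumption about the number of surgeons, the number of centres or the outcome variance.

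The point is minor. One of three named levels in one secondary analysis is affected. The primary comparison, sample size, randomisation and data collection are not touched. No numerical bias can be attached to it, because the harm arises only if surgeon-level figures are reported and read as effects of the approach.

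**What to change.** Replace the clause with wording such as:

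*A secondary mixed model with random centre, random surgeon (nested in arm within centre) and a random centre-by-treatment term will give one overall treatment effect, together with the variance components: between surgeons within arm, between centres, and between centres in the treatment effect. Because each surgeon performs one type of operation, no surgeon-level treatment effect is estimated.*

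One check belongs with this. If a centre has a single surgeon in each arm, its surgeon and centre-by-treatment variation cannot be told apart. The variance components should therefore be reported with the number of surgeons per arm in each centre.

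The cost is one sentence, with no new data. The downside is giving up a stated estimate that the design cannot deliver.
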